**16. Ethical and legal aspects**

The study is conducted according to the current version of the Declaration of Helsinki of the World Medical Association and the ethical principles for research on humans.

The study protocol will be submitted to the responsible ethics committee of the medical faculty Heidelberg for evaluation before the beginning of the study. It will not be started with the inclusion of study participants unless the written affirmative vote of this ethics committee is available.

Until the inclusion of the patients or their family members for the follow-up, the study serves to ensure quality assurance of the consultation quality of the pharmacy staff in the participating community pharmacies. The demonstration of the application by the medication user and the following consultation by the pharmacist can already take place during routine counseling. The pharmacy staff will document the work load within this quality-assuring project, for example additional time effort or interruption of work routine for evaluating the feasibility for daily use of the training. If patients or their family caregivers do not agree to participate in the study, the data on medication administration that was collected during the consultation might be used for

[figure not shown]

evaluation of the consulting quality. Pseudonymization does not happen because there is no follow-up for these patients or their family caregivers.

The participation of all participants in this study is voluntary.

The pharmacy staff of the participating community pharmacies will be informed in written and oral form before the beginning of the study about the nature and scope of the planned intervention, in particular about the possible benefits and risks or burdens, the voluntariness of the participation and about the required documentation of their approval by signing the declaration of consent. To cluster the educated medication users not only according to the community pharmacy but also according to the educating person, the pharmacy staff will get a pseudonym which indicates their profession (e.g. pharmacist or pharmacy technician) and their professional experience (less than a year, 1-5 years, more than 5 years).

The patients and family caregivers will be informed in written and oral form after the training about the nature and scope of the planned follow-up visits, about the possible benefits and risks or burdens, the voluntariness of their participation and about the documentation of their approval by signing the declaration of consent.

The information document informs the study participants (patients, family caregivers and pharmacy staff) about data collection which is carried out in a pseudonymized form. Furthermore, patients and family caregivers will be informed that the data collected up to the time of inclusion will be pseudonymized when they are included in the study to enable an assignment of the follow-up visits. The pharmacy staff can only transfer the corresponding patient identification number to the data collected up to this moment if the patient agrees immediately after the conducted consultation and data collection to participate in the follow-up visits. If the patient is not able to do that, he will not be included in the study. At the time of scientific publication, data are pseudonymized for the staff of the department of Clinical Pharmacology and Pharmacoepidemiology, and the data is actually anonymized for third persons at any time. The approval of the participants of the study can be withdrawn at any time without declaring any reasons and without any disadvantages for further medical treatment. If the approval is withdrawn, it will be decided together with the study participant whether he agrees to the evaluation of the collected data up to this moment; otherwise his data will be deleted. If individual members of the pharmacy staff withdraw their consent, the study can be continued in the pharmacy with the pharmacy staff still participating.

[figure not shown]

The names of the study participants and every confidential information is bound to professional discretion according to the penal code (StGB), the professional codes of discretion and the regulations of the German Data Protection Act (BDSG).

For the evaluation, data (e. g. names and other personal information) will be pseudonymized. Data of participants will only be passed on in a pseudonymized form as the case may be. Third persons will not gain any insight into study documents which contain non-anonymized personal data. The results will be published in a consolidated way without indicating any names or other personal data of the participants. Data and documentation papers will be archived on the central secured server of Heidelberg University Hospital.

[figure not shown]

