##### **Secondary outcomes**

- Rate of incorrect medication administration before and after patient education in the control and intervention group.
- Rate of incorrect medication administration during the course of follow-up visits.
- Influence of the consideration of the individual level according to the Transtheoretical Model [20] on the willingness to participate in a training, i.e. long-term (1, 6 and 12 months) correct drug use.
- Univariate and multivariate analyses to evaluate the influence of covariates such as dosage form, patient characteristics, the training person and the number of medicines on training success.
- Qualitative: feasibility of implementation in community pharmacies, satisfaction of patients and caregivers.

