## **11. Study procedure**

The study will be carried out in community pharmacies with which other projects have already established cooperation. Prior to the start of the study, pharmacy staff will be informed of erroneous and correct administration of the different dosage forms (see inclusion criteria) known from the literature, the use of study materials, and the study procedure. After written informed consent of the head of the pharmacy and pharmacy staff, the pharmacies will be assigned to control or intervention group (cluster randomization). There will be exclusive control pharmacies and intervention pharmacies.

Pharmacy staff addresses potential study participants according to the inclusion criteria during daily routine in the community pharmacy. It is possible within the scope of this study to train the use of different dosage forms for the same patient or family caregiver. In order to identify a potential administration error, the pharmacy staff asks the patient or family caregiver to use the medicine (duration approx. 2-5 minutes). Such a demonstration is quite common in the context of the usual pharmaceutical counseling. The demonstration can be performed with the patient's drug itself or with a placebo. The pharmacy staff assesses a possibly incorrect administration by using a checklist defined in advance for a specific dosage form. Checklists and placebo materials are provided by the Department of Clinical Pharmacology and Pharmacoepidemiology. In the control group, pharmacy staff provides a standard consultation (duration approx. 3 minutes) followed by the provision of standardized information material, e.g. written step-by-step

instructions. In the intervention group, the staging algorithm (Fig. 1) is used to determine the individual level of the patient or caregiver according to the Transtheoretical Model. The stage "Maintenance", i.e. the permanent correct use of the drug, cannot be detected with this algorithm. The purpose of this model is to identify in particular those medicines users who are not aware of administration errors despite incorrect use of the drug and who may not be motivated to seek training or detailed counseling.

[figure not shown]

Figure 2. Staging Algorithm

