Patients or caregivers who are in a “pre-action stage” (i.e., precontemplation, contemplation, and preparation) will be informed and trained by the pharmacy staff about the use of the drug according to their individual level (Table 1) (approximately 5-10 minutes).

Table 1. Possible level-specific interventions.

| Stage of change   | Study-specific definition | Possible intervention                                                          | Example                                                                                                                              |
|-------------------|---------------------------|--------------------------------------------------------------------------------|--------------------------------------------------------------------------------------------------------------------------------------|
| Pre-contemplation | Lack of error awareness   | e.g. create awareness of the problem, point out risks of incorrect application | Presentation of a risk score, information about possible consequences of incorrect application and advantages of correct application |
| Contemplation     | Aware of an error         | e.g. point out the risks of incorrect application, show possibilities          | Proposal for a training                                                                                                              |

|             |                                            |                                                                 |                                                                                                           |
|-------------|--------------------------------------------|-----------------------------------------------------------------|-----------------------------------------------------------------------------------------------------------|
| Preparation | Aware of an error, search for solutions    | e.g. standardized education materials for specific dosage forms | Education based on standardized information materials                                                     |
| Action      | Drug is administered correctly             | e.g. regular monitoring                                         | Follow-up visits with re-presentation of the application, assessment by the pharmacy staff and retraining |

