| Maintenance | Drug is permanently administered correctly | e.g. regular monitoring                                         | Follow-up visits with re-presentation of the application and assessment by the pharmacy staff             |

Immediately after the training (intervention group) or after issuing the standardized instructions (control group), the drug application is checked again using the checklist. If errors continue to occur, there will be a corresponding retraining in the intervention group. In the control group, the patient or family caregiver is made aware of the errors verbally.

After the pharmaceutical consultation that can represent a standard situation in community pharmacies, the patients or caregivers are invited to participate in the follow-up visits. Study information is provided by the pharmacy staff or staff of the department of Clinical Pharmacology and Pharmacoepidemiology. If the patient or caregiver wishes to participate in the study and attests this by his written consent, his so far anonymized data will be pseudonymized. After inclusion in the study, patients and caregivers are asked to answer a sociodemographic questionnaire (duration approx. 5 minutes). In addition, e.g. finger strength and cognitive abilities may be considered as factors influencing the training success. Further data collection during follow-up visits is pseudonymized. Within the study, three follow-up visits will be planned at 1 month, 6 months and 12 months. Patients or caregivers are either referred to the follow-up at the pharmacy at the appropriate time or contacted by pharmacy staff or staff of the department of Clinical Pharmacology and Pharmacoepidemiology. Patients or caregivers can choose the preferred way of contacting, e.g. call, email or letter, prior to inclusion into the study. At follow-up visits the patient or family caregiver will be asked to demonstrate again drug administration, which is evaluated by the pharmacy staff or staff of the department of Clinical Pharmacology and Pharmacoepidemiology using the checklist. In the case of incorrect application, re-training takes place again. During the follow-up visits, patients and caregivers might be contacted by pharmacy staff or staff of the department of Clinical Pharmacology and Pharmacoepidemiology, e.g. by

[figure not shown]

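### Users are invited and consent only after the arm-specific counselling and re-check, so entry to the primary 6-month comparison may depend on the arm

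*Protocol*

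**What the plan says.** Section 11 of the protocol (Study procedure) fixes the order of events.

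1. Pharmacies are allocated before any user is approached: "There will be exclusive control pharmacies and intervention pharmacies".
2. Staff of the allocated pharmacy recruit: "Pharmacy staff addresses potential study participants according to the inclusion criteria during daily routine in the community pharmacy". The user demonstrates the medicine, and staff score it on a checklist.
3. The arms then differ. Control users get a standard consultation of about 3 minutes and written material. Intervention users are staged, and those in a pre-action stage "will be informed and trained by the pharmacy staff about the use of the drug according to their individual level", in about 5 to 10 minutes.
4. The checklist is repeated in both arms. Remaining errors lead to retraining in the intervention arm and to a verbal pointer in the control arm.
5. After this, "the patients or caregivers are invited to participate in the follow-up visits".

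Section 16 (Ethical and legal aspects) confirms the timing. Patients and caregivers "will be informed in written and oral form after the training about the nature and scope of the planned follow-up visits", and a user who cannot agree immediately after the consultation is not included. People who decline have no follow-up. Of their consultation results, the protocol says only that "the data on medication administration that was collected during the consultation might be used for" evaluating the quality of the counselling.

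The primary outcome (section 4) is the error rate by arm at 6 months, compared by chi-square test (section 15).

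**The concern.** Randomising pharmacies protects the comparison only if the people analysed in each arm are not selected through something the arm itself influences. Here the decision to enter follow-up comes after a contact that differs by arm in length, in content and in how remaining errors are handled. When users decide, they have also just been through a repeat demonstration. All of this could plausibly bear on willingness to return and on later correctness.

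If the link between consenting and later correct use differs between arms, the 6-month comparison mixes the effect of the training with the effect of who agreed to come back. That could create a difference where there is none, or hide a real one. A chi-square test on those who entered cannot separate the two.

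**Working it through.** **Order of events.** Allocation, demonstration, arm-specific counselling, re-check with arm-specific handling of errors, invitation, immediate consent or exclusion, 6-month outcome. No section places a participant's consent before the counselling. The inclusion criterion of written consent (section 8) gives no timing and so does not contradict this order.

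**The plan's own figure.** Inputs from section 15: success rates 32% and 52%, alpha 0.05 (taken as two-sided), power 80%, ICC 0.02, drop-out 15%. With the variance pooled under both hypotheses:

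n = (1.96 + 0.84)² × 2 × 0.42 × 0.58 / 0.20² = 95.6 per group

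- 95.6 × (1 + 4 × 0.02) / 0.85 = 121.5, rounded up to 122.
- 95.6 × (1 + 9 × 0.02) / 0.85 = 132.7, rounded up to 133.

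Both stated figures reproduce when 5 and 10 are used as administrations per pharmacy. Whether that matches the text is a separate matter. What counts here is that the test has about 96 effective observations per arm, and that the 15% covers loss after inclusion, not selection into the study.

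**Effect of selective consent (illustration).** Let p be the true 6-month success rate in an arm, a the consent rate among users who would succeed, and b the rate among those who would fail. The success rate observed among consenters is

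p_obs = p·a / (p·a + (1 − p)·b)

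If a = b, then p_obs = p. A different overall consent rate does not bias the comparison by itself; a different link between consent and outcome does. All values of a and b below are assumptions. Consent in the control arm is taken as unrelated to outcome, so control stays at 32%.

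*No true effect (32% in both arms):*

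| a / b, intervention | Observed, intervention | Apparent gap | Rejection rate |
|---|---|---|---|
| 80% / 80% | 32.0% | 0 | 5% |
| 80% / 70% | 35.0% | 3.0 points | 7% |
| 80% / 60% | 38.6% | 6.6 points | 16% |
| 80% / 50% | 43.0% | 11.0 points | 35% |

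Third row: 0.32 × 0.80 / (0.32 × 0.80 + 0.68 × 0.60) = 0.256 / 0.664 = 0.386.

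*True rates 32% and 52%, selection in the other direction:*

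| a / b, intervention | Observed, intervention | Expected gap | Power |
|---|---|---|---|
| 80% / 80% | 52.0% | 20.0 points | 81% |
| 70% / 80% | 48.7% | 16.7 points | about 65% |
| 60% / 80% | 44.8% | 12.8 points | about 45% |
| 50% / 80% | 40.4% | 8.4 points | about 22% |

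Third row: 0.52 × 0.60 / (0.52 × 0.60 + 0.48 × 0.80) = 0.312 / 0.696 = 0.448.

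Rejection rates and power use the normal approximation to the two-sided chi-square test with 96 effective observations per arm.

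**The case against.** - **No evidence that consent differs by arm.** The protocol gives no consent rates, and selection could be negligible. This stands. The text shows that the route is open, not that it is used.
- **The trial's own hypothesis.** A reader might infer that the protocol itself predicts differential consent, because a secondary outcome concerns the influence of staging "on the willingness to participate in a training". That outcome is about willingness to be trained, which the protocol links to long-term correct use. It is not about agreeing to study follow-up and does not support the inference.
- **The arms are less different than they look.** Control users also get the re-check and are told of remaining errors, and the longer training is only for users in a pre-action stage. This makes strong selection less likely but leaves the contacts before consent different.
- **Late consent has a purpose.** Section 16 treats everything before inclusion as quality assurance of routine counselling. The intervention is aimed particularly at users unaware of their errors. A consent talk first could deter or prime them and would disturb the setting whose feasibility is being studied. This is a real cost, and it is why earlier consent should not be the only remedy.
- **This belongs in the SAP.** The SAP is not shown, and it may define analysis populations and weighting. It cannot re-order consent, and it cannot use data on people who declined unless the protocol provides for recording them for that purpose.

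**Conclusion.** The concern holds as a risk to the primary comparison. Under the plan as written, only users who consented after exposure to their arm's counselling can contribute a 6-month outcome, and nothing in the protocol's analysis addresses this.

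The size and sign of any bias cannot be derived from the document. Under the assumed rates it ranges from none to a false gap of 11.0 points, or to a loss of 11.6 points (20.0 − 8.4) from a true 20-point effect. These figures depend wholly on the assumed consent rates, on an undisturbed control arm, and on the link between consent and outcome differing between arms.

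A reader might go further and conclude that the arms are not comparable. The protocol supports only that they may not be. A reader might also conclude that nothing can be done in the analysis. Weighting can reduce selection on measured factors, though not on unmeasured ones.

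**What to change.** **1. Whatever the timing of consent (sections 15 and 16).** Replace the optional wording on non-consenters' data with a commitment to record, by arm, the anonymised baseline and immediate re-check checklist results of every counselled user. Widen the stated purpose beyond counselling quality if needed. Then:

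- report the consent rate and baseline error rate by arm;
- compare the immediate re-check between arms in all counselled users, as a supportive analysis that consent cannot distort;
- add a sensitivity analysis of the 6-month result weighted by the probability of consent given arm, dosage form, baseline result and re-check result, stating that it corrects only for selection on these factors. The sociodemographic questionnaire is completed after inclusion, so it cannot inform the weights.

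The cost is modest: the checklists are already completed during the consultation. The wording on data use may need an amendment.

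**2. Where feasible (sections 11 and 16).** Place information and consent for follow-up after the baseline demonstration and before the standard consultation or staging, and analyse everyone who consented at that point. This removes selection caused by the counselling. It costs a protocol and information-sheet amendment, possible extra refusals, some priming of users unaware of their errors, and some departure from routine practice.

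Neither step prevents selective approaching by staff who know their pharmacy's arm. The report should state that limitation.
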